## Abstract

**Background:**

Instrumental activities of daily living (iADLs) are crucial for older adults to live independently. Health care and technological advancements will increase the older adult population and life expectancy globally. Difficulties with iADLs impact older adults’ quality of life. Mobile apps can assist older adults, but many require help due to limited awareness. Lack of awareness is a barrier to app use. Existing literature mainly covers health care and app design, needing more focus on iADL apps for older adults.

**Objective:**

The study objectives encompass 2 main aspects: first, to evaluate the awareness, use, and factors influencing the use of apps among older adults for iADLs; and second, to create and assess the effectiveness of a gerontechnology empowerment program (GEP) for older adults on the awareness and use of apps for iADLs.

**Methods:**

This research uses a quantitative approach divided into 2 distinct phases. In phase 1, we conduct a descriptive survey to assess the level of awareness and use of mobile apps for iADLs and identify the factors that influence the use of such apps among older adults. To ensure clarity and comprehension among participants, we provide them with a subject information sheet in both Kannada and English. The data collected during this phase enable us to gain insights into awareness levels, use patterns, and factors that shape older adults’ use of apps for iADLs. The results serve as the foundation for designing the GEP. In phase 2, a cluster randomization method will be used to select older adults aged 60 to 75 years in Udupi district, Karnataka, India, who are active smartphone users. These participants will be divided into 2 groups: the experimental and the control groups. The experimental group will join the GEP. The sample size for phase 1 is 554, and phase 2 is 50. To assess the effectiveness of this program, we will measure the outcomes before and after its implementation using the same assessment tools used in phase 1.

**Results:**

This study is funded by the Indian Council of Medical Research (Adhoc/193/2022/SBHSR on November 18, 2022). Phase 1 data collection is expected to be completed by November 2023, and phase 2 is scheduled to commence in the upcoming months. Phase 1 and 2 findings will be analyzed and discussed in the main paper, which we intend to submit to a high-quality peer-reviewed journal for publication. The research protocol, informed consent forms, and associated documentation received approval from institutional ethics committees (214/2020).

**Conclusions:**

Upon the successful testing of the GEP, it can be recommended that welfare departments encourage older adults to use mobile apps for iADLs and establish training programs to provide support to older adults in using these apps.

**Trial Registration:**

Clinical Trials Registry - India CTRI/2020/09/027977; https://ctri.nic.in/Clinicaltrials/pmaindet2.php?EncHid=NDUxMzM=&Enc=&userName=027977

**International Registered Report Identifier (IRRID):**

DERR1-10.2196/53587

## Introduction

### Background

Advancements in health care, lifestyle improvements, and technological progress are poised to elevate the global average life expectancy from 72.6 to 77.1 years by 2050, with India also experiencing a similar upward trajectory. In 1960, India had an overall life expectancy of merely 40 years, but today, it stands at approximately 69 years [1]. Forecasts indicate a continued increase in life expectancy in the coming decades [2]. According to a United Nations report, India’s older adult population is expected to grow substantially, reaching 19% by 2050 in contrast to the global average of 22%. Consequently, the aging demographic will encounter significant challenges in both activities of daily living (ADLs) and instrumental activities of daily living (iADLs), including tasks like communication, shopping, medication management, financial handling, travel, meal preparation, cleaning, and laundry [3]. This, in turn, will considerably impact older adults’ overall quality of life (QOL). Given these evolving trends, it becomes increasingly crucial for researchers and practitioners to identify cost-effective, feasible, and practical strategies to mitigate or prevent any decline in ADL and iADL abilities among older adults [4].

Experts consider the judicious use of technology as a facilitator and a potential solution for enhancing the QOL among the older population [5]. Specifically, mobile technologies and smartphones have proven highly effective in assisting older adults in self-management and prosperous living by providing them with increased access to relevant, valuable, and timely information for efficient self-governance, addressing ADLs and iADLs [6]. However, despite a growing inclination among older adults in India toward adopting mobile-related technologies, it is evident that they need help with mobile technology adoption [7]. Nevertheless, these challenges tend to diminish with the continuous use of mobile and related technologies, eventually becoming an integral part of their lives, aiding them in ADLs and iADLs [8]. Recognizing that smartphone technology use tends to be more prevalent among younger individuals, experts emphasize the importance of research that explores the motivations and barriers influencing smartphone and related technology use among older adults. This research is crucial because older adults stand to benefit as much, if not more, from technology compared to younger adults [9].

Considering the abovementioned observations, this research addresses these gaps by focusing on older adults. It aims to assess their awareness and use of mobile apps for iADLs, pinpoint the factors that drive or inhibit their use, and ultimately establish a sustainable gerontechnology empowerment program (GEP) based on the empirical findings [10]. This program aims to enhance and empower older adults’ propensity, interest, adoption, and use of the latest mobile apps designed for iADLs. This study is rooted in several interconnected areas, including the anticipated rise in the older adult population, the potential advantages of mobile apps in aiding iADLs, the factors influencing their adoption among older adults, and the empowerment of older adults in using mobile apps for iADLs. The demographic landscape of our world is undergoing a significant transformation, with older adults playing an increasingly substantial role. Older adults account for approximately 11.5% of the global population, projected to surge to 22% by 2050 [3]. The importance of iADLs in the lives of older adults cannot be overstated. These activities are notably more intricate than the basic ADLs and are pivotal for older adults to maintain their independence [11].

### Significance of the Study

In the context of ADLs, it is noteworthy that, as of 2011, around 7.6% of older adults in India faced difficulties in performing them. However, the distinction between ADLs and iADLs becomes more evident when we consider that iADLs demand heightened expertise, decision-making abilities, skills, and individual discretion compared to the tasks associated with ADLs [1]. The challenges older adults encounter in managing iADLs are well-documented by research, consistently affirming the previously mentioned perspective [11]. Studies have shown that older individuals experience escalating difficulties in food preparation, shopping, handling telephones and related devices, and basic laundry [12]. These challenges underscore the pressing need for research and intervention to facilitate the adoption of technology, particularly mobile apps, to empower and support older adults in their pursuit of independent living [7]. Older adults’ use of technology, including computers and the internet, is influenced by various factors, including age, education, and attitudes toward technology [13]. Previous research has consistently shown that age is a strong negative predictor of technology use, suggesting that older individuals tend to be less inclined to embrace technological advancements [14].

In the context of developing countries, mobile phones, mobile apps, and related technologies have emerged as crucial components of information and communication technology (ICT) systems designed to assist individuals of all ages [15]. These technologies have found significant use, particularly in the health care sector. Mobile apps, as integral components of mobile health (mHealth) interventions, offer a wide range of benefits, such as assessing fall risks in home settings for older adults [14]. Mobile phones also play a vital role in supporting telemedicine and providing remote health care services in developing nations [16].

The advent of net banking has brought about advantages for older adults, including 24-hour access, flexibility, independence, and the ability to overcome physical barriers associated with age in accessing financial services. Similarly, mobile apps related to food preparation, such as recipes and diet apps, as well as service-oriented apps for housekeeping, laundry, and cleaning, have the potential to enhance various aspects of older adults’ lives. However, despite the widespread adoption of mobile phones and related technologies and their proven potential to improve services like health care, banking, and travel, these technologies’ adoption, acceptance, and use among older adults remain notably low [17].

Mobile phones and related technologies and apps have demonstrated their capacity to significantly enhance the QOL for older adults in areas such as health care, commerce, independent living, reduced isolation, strengthened connections with family and friends, and more [9,18].

Connecting with loved ones through technology contributes to higher mental and physical well-being. Notably, technology use for nonsocial purposes is linked to enhance the overall physical well-being, while its social use mitigates the negative impact of loneliness on overall life satisfaction [19]. Consequently, mobile phones and related technologies and apps extend beyond mere communication devices; they have a profound societal impact by liberating us from geographical constraints.

Despite older adults demonstrating a generally positive attitude toward technology, they often encounter complexities. Additionally, demographic characteristics such as age, gender, and education level play crucial roles in predicting their adoption of mobile technology [20]. Understanding the motivations and obstacles behind older adults’ behavior regarding the use of mobile apps is essential [9].

In the context of mHealth adoption among older adults in a developing country, a study applied parameters from the well-established unified theory of acceptance and use of technology framework along with 2 additional variables: technology anxiety and resistance to change. The study revealed that factors such as performance expectancy, social influence, technology anxiety, effort expectancy, and resistance to change significantly influenced older adults’ behavioral intentions to use mHealth. Interestingly, facilitating conditions did not substantially affect behavioral purposes [17]. This underscores the importance of considering the perceived benefits and ease of use and factors like anxiety and resistance to change when designing interventions to promote technology adoption among older adults.

A randomized controlled trial was implemented on smartphone use training programs among older adults and found a positive effect on smartphone use skills and overall QOL. This underscores the importance of providing detailed instructions and guidance to older adults by technology and service providers to cultivate favorable perceptions and confidence in using new technology [10]. Furthermore, any training program designed for older adults to promote the practical use of mobile apps is expected to result in significantly lower depressive symptom scores than baseline measurements. Additionally, it is anticipated that such programs will facilitate the use of mobile apps for various purposes, including health management, entertainment, transportation, and social media interaction, thereby contributing to the overall well-being of older adults [21]. While the impact of ICT on ADLs has been acknowledged, more research needs to examine the influence of ICT on iADLs [22]. Given the increasing older adult population, there is a pressing need for a comprehensive understanding of effective empowerment and training interventions tailored to their unique needs [23]. This will be instrumental in improving their QOL and enabling them to lead more independent and fulfilling lives. With this study, we would like to contribute to achieving the Sustainable Development Goal (4.3.2) by educating the general public and encouraging lifelong learning.

### Novelty

This study intends to fill the following gaps in the literature: (1) While there is substantial literature on mobile technology and apps for older adults in the context of their iADLs, existing studies predominantly emphasize health care, app features, design considerations, and overall effectiveness. (2) This study uniquely focuses on using mobile apps by older adults to facilitate their performance of iADLs. (3) The GEP represents a pivotal aspect of this research, aiming to foster awareness and encourage the use of mobile apps among older adults. (4) This program empowers older adults to effectively perform their iADLs through technology.

### Objectives

The objectives of the study are to assess the awareness and factors influencing the use of mobile apps among older adults for iADLs and to develop and determine the effectiveness of a GEP for older adults on awareness and use of mobile apps for iADLs.

## Methods

### Research Design

The research design for phase 1 is cross-sectional descriptive research, and phase 2 is a cluster randomized control trial. The Indian Council of Medical Research Guidelines for Extramural Research was adopted to prepare the funding proposal [24].

### Participants

The participants in this phase exclusively consist of older adults aged between 60 and 75 years who use smartphones and are affiliated with welfare organizations associated with the District Disabled Welfare Office in Udupi district, Karnataka state, India. Additionally, participants must be able to read and write in English and express a willingness to participate in the study. Nonsmartphone users will be excluded from this research study.

### Sample Size

Sample size calculations were performed separately for phase 1 and phase 2 of the study. For phase 1, a sample size of 369 participants was estimated based on proportion values. This sample size was then adjusted by a design effect of 1.5 to account for potential clustering or stratification, resulting in a required sample size of 554 participants. In phase 2, the focus was on comparing 2 proportions. To ensure the study’s robustness in the face of potential dropouts (estimated at 20%), an initial sample size of 31 participants was calculated for each group. This initial size was adjusted by a design effect of 1.5 to consider the study’s specific design characteristics, yielding a total required sample size of 46 participants per group, rounded up to 50 participants per group.

### Ethical Considerations

The research protocol, informed consent forms, and associated documentation received approval from the institutional ethics committee (214/2020) of Kasturba Medical College and Kasturba Hospital Institutional (Registration no.: ECR/146/Inst/KA/2013/RR-19). This study is also registered under the Clinical Trials Registry - India (CTRI/2020/09/027977). In this study, participants will receive a subject information sheet in both Kannada and English to help them understand the study. The data will be collected only after informed consent is obtained. The confidentiality and anonymity of the participants will be maintained.

### Recruitment

This study is structured around a 2-phase research design (Figure 1). The sample was selected purposively from welfare associations of the Udupi district. Phase 1 was initiated after the ethics and Clinical Trials Registry - India approval. For the study’s second phase, the sample will be randomly allocated to experimental and control groups from various welfare organizations of the Udupi district. We have planned to use the clustered randomization process to select participants based on the study’s eligibility criteria.

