### Data Collection Plan

The study is in progress by visiting older adults’ welfare organizations after obtaining prior approval. In phase 1, participants will receive a subject information sheet in both Kannada and English to explain the study details. Data will be collected using a structured questionnaire, with participants’ consent, to assess their awareness and the factors influencing the use of mobile apps for iADLs. In phase 2, cluster randomization will be used to select older adults for the experimental or control groups. The GEP will be administered to the experimental group. The effectiveness of the GEP will be assessed through measurements taken before and after its implementation.

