#### Develop and Determine the Effectiveness of a GEP

The GEP will be a comprehensive intervention designed to facilitate the use of smartphone apps for iADLs. The development of GEP will be based on the findings from the study’s first phase, incorporating insights from experts in health care, mobile technology, and older adults’ welfare departments or organizations. The structure of the GEP program will encompass the following components: information and features—detailed information about smartphone apps relevant to iADLs, including their features and functionalities; installation procedures—step-by-step guidance on installing and setting up these smartphone apps; general awareness—fundamentals of smartphone use and general awareness regarding its capabilities; security awareness—guidelines on ensuring smartphone security and safe use; dos and don’ts—best practices and precautions for effective and responsible smartphone use; operation manuals—manuals provide instructions on operating specific smartphone apps for iADLs. The training program will be conducted through 8 sessions, each lasting 3 hours. These sessions will incorporate hands-on training using audiovisual facilities to enhance participants’ understanding and practical skills in using smartphone apps effectively for iADLs.

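### The article uses cluster randomisation to describe both selection and allocation of phase 2 participants, so recruitment into an already known arm is not excluded

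*Protocol article*

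**What the plan says.** Under Research Design, "phase 2 is a cluster randomized control trial". Three places then give randomisation the job of choosing people:

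- Abstract, Methods: "a cluster randomization method will be used to select older adults aged 60 to 75 years in Udupi district".
- Recruitment: "We have planned to use the clustered randomization process to select participants based on" the eligibility criteria.
- Data Collection Plan: "In phase 2, cluster randomization will be used to select older adults for the experimental or control groups".

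Two adjacent sentences describe a different order. In the Abstract, the sentence after the one quoted is "These participants will be divided into 2 groups: the experimental and the control groups". In Recruitment, the sentence just before the one quoted says that the phase 2 sample, drawn from several welfare organisations, will be allocated at random to the two groups.

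On timing, Ethical Considerations places consent before data collection, and the Data Collection Plan places the first measurement before the programme is delivered. Neither is tied to the moment of allocation. The Participants section lists willingness to take part among the entry requirements. On the programme itself: "The training program will be conducted through 8 sessions, each lasting 3 hours".

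**The concern.** Random allocation decides which arm a cluster joins. It does not apply eligibility criteria or choose members. When the two steps are described as one, the text can be followed in a way that draws the allocation first and then looks for eligible, willing people for an arm that everyone already knows.

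In a cluster trial one draw settles the arm for a whole organisation, so anyone approached afterwards can know what is on offer. A training course cannot be concealed from the people invited to it. If the offer affects who says yes, the experimental arm may contain more people who already want to learn apps. Such people may improve in awareness and use without the programme, and those are the outcomes. Randomising organisations does not protect against this, because the difference arises within organisations after the draw. It also cannot be undone once enrolment is complete.

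**Working it through.** The point concerns the order of steps, so the main check sets the statements side by side.

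| Place | What happens to people | Order implied |
|---|---|---|
| Abstract, Methods, first sentence on phase 2 | selected by cluster randomisation | selection and allocation are one step |
| Abstract, Methods, next sentence | divided into two groups | selection, then allocation |
| Recruitment, sentence before the quote | an existing sample is allocated | selection, then allocation |
| Recruitment, quoted sentence | selected by randomisation according to eligibility | selection and allocation are one step |
| Data Collection Plan | selected for one arm or the other | the arm can be known at selection |
| Ethical Considerations | consent before data collection | silent on allocation |
| Data Collection Plan, on measurement | baseline before the programme | silent on allocation |

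The statements do not agree on one order, and none excludes recruitment after the draw. None says who knows the allocation at enrolment.

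**Conditions for bias.**
1. The offer is substantial: 8 × 3 h = 24 h of training.
2. Participation is voluntary (Participants).
3. The outcomes are awareness and use of apps, taken by questionnaire (Abstract; Research Instrument).
4. Motivational factors and barriers are recorded (Research Instrument), and the Abstract says that phase 2 uses the phase 1 tools before and after the programme. An imbalance could therefore be seen. The effectiveness tests under Plan for Data Analysis (repeated measures ANOVA, *t*, Mann-Whitney, Wilcoxon, χ²) name no adjustment for it.

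**What drives the size.** With a simple split into motivated and other participants:

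bias = (share motivated, experimental − share motivated, control) × (extra improvement of motivated people without the programme)

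The documents give none of these quantities. With purely assumed values:
- (0.70 − 0.50) × 0.30 = 0.06, or 6 percentage points
- low: 0.10 × 0.20 = 0.02, or 2 points
- high: 0.30 × 0.40 = 0.12, or 12 points

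These show how the formula behaves and are not estimates for this trial. The number of participants does not appear in the formula.

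**The plan's own figure.** Sample Size gives 31 per group with a design effect of 1.5: 31 × 1.5 = 46.5, against the stated 46, rounded up to 50. The figure reproduces to within one participant. The design effect allows for extra variance from clustering and does nothing about who is recruited.

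**The case against.** The strongest reply is that this is loose wording in a condensed article. Selecting by cluster randomisation may simply mean taking eligible members of organisations that were drawn at random, and the two adjacent sentences support selection first and division second. The exact sequence, and any shielding of recruiters, would commonly stand in the full protocol, which is not shown. The research framework figure is not visible either.

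Much of this stands. Silence on the order is not counted against the article. What remains is what it does state: the same merging of two steps in three places, once with the arm named, beside sentences that describe another order. That is a contradiction in the text and not only an omission.

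Several stronger readings are tempting and are not supported:
- A reader might infer that eligibility, consent and baseline do follow a known allocation. No sentence says so, and two point the other way.
- A reader might infer that controls are offered questionnaires only. The article does not say what controls are offered, and a later offer of the programme is neither stated nor excluded.
- A reader might take the willingness requirement as willingness to enter a particular arm. It reads as ordinary voluntary consent to the study.
- A reader might treat motivation as unmeasured. It is measured, although measured scores need not capture all self-selection, and the absence of a named adjustment could be settled in an analysis plan that is not shown.

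**Conclusion.** The concern holds in limited form. The article merges selection with allocation, is inconsistent about their order, and leaves recruitment after a known allocation open. If recruitment did run that way, motivation could differ between arms and a difference in favour of the programme could partly reflect who joined. Whether it will run that way is not known, and confidence on the actual order is moderate.

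No size can be given from the documents. The 2 to 12 points above rest wholly on assumed inputs and should not be cited as an expected bias. The conclusion assumes that the clusters are the welfare organisations, which Recruitment suggests without saying so directly, and that invitees could learn their arm once the draw is made.

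**What to change.** Reword the Abstract, Recruitment and Data Collection Plan so that randomisation allocates organisations and does not select participants. State one order for phase 2:

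1. List the participating organisations.
2. In every one of them, screen members, obtain consent with a single information sheet that describes both arms, and complete the baseline questionnaire.
3. Close each organisation's participant list.
4. Only then draw and disclose the allocation of organisations.

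If this order is not feasible, state how recruiters and invitees are kept unaware of the allocation until enrolment.

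The cost is revised wording and a change in the order of visits. Screening, consent and baseline are needed in any case. The downside is a short wait between baseline and the first session. The article reports phase 2 as still to start, so the change can be made in time.
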